Can the combination of the face-to-face group-based intervention MoVo-LISA and MoVo-App increase maintenance of the initiated physical activity level in patients with musculoskeletal disorders more than MoVo-LISA without subsequent MoVo-App use?

We hypothesize that the additional MoVo-App can help to maintain the initiated level of physical activity (by the face-to-face group program) 6 months after clinic discharge in patients with musculoskeletal disorders more than MoVo-LISA without the app.

The following are secondary research questions:
2.Can the combination of MoVo-LISA and MoVo-App improve cognitive mediators of behavioral change (e.g., self-efficacy or action planning), and health-related variables (e.g., pain intensity, depression) in patients with musculoskeletal disorders more than the same face-to-face group-based intervention without subsequent MoVo-App use?3.Which cognitive and sociodemographic factors moderate and mediate the effects of MoVo-LISA and MoVo-App?

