**Fig. 1 Fig1:**
[figure not shown]
Schedule of enrollment, interventions, and assessments

This is a multicenter, pragmatic RCT of parallel design with an allocation ratio of 1:1. In this RCT, we aim to evaluate whether the MoVo-App in combination with the group-based face-to-face intervention MoVo-LISA during orthopedic rehabilitation can effectively support inactive individuals to initiate physical activity, to increase their amount of physical activity (minutes per week), and to maintain this level of physical activity (physically active: yes/no and minutes per week) in the long term.

All participants receive treatment as usual (TAU) and the face-to-face group-based intervention MoVo-LISA during their clinic stay (*see* Fig. 1 and the Consolidated Standards of Reporting Trials (CONSORT) flowchart in Fig. 2). After participating in the face-to-face MoVo-LISA program in the clinic, the IG receives the MoVo-App at clinic discharge as a blended intervention. Following eligibility screening by the clinic staff, participants give informed consent and complete baseline outcome assessments prior to randomization and allocation (T0). Assessments are repeated at clinic discharge (T1), at 6 weeks (T2), and at 4 months after discharge (after the end of the MoVo-App and thus post-treatment) (T3), as well as 6 (T4) and 12 months (T5) after discharge (follow-up). All assessments are conducted through online questionnaires. The first two assessments (T0 and T1) take place in the clinic, and the participants are supported by a study assistant. All further online questionnaires are sent to the participants via e-mail. If the participants do not complete the questionnaires, they will be reminded after 2, 4, 6, and about 14 days after receiving the questionnaire. The first and second reminders are sent to the participants by e-mail. The third reminder is carried out via telephone. If the patients cannot be reached by telephone, they are called a second time.

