### Inclusion criteria

Patients are included if they fulfill the following inclusion criteria: (1) age 18 years or older; (2) musculoskeletal diagnosis classified in chapter M of the International Statistical Classification of Diseases and Related Health Problems, 10th Revision (ICD-10) [42], diagnosed by a physician; (3) sufficient knowledge of the German language; (4) ownership of a smartphone and internet access for online assessments; and (5) being physically inactive (sport activity < 30 min/week) in the last 3 months. Exclusion criteria are (1) rehabilitation following inpatient clinic treatment (e.g., due to surgery) and (2) not able to exercise for medical reasons. Eligible patients receive an invitation to participate in the study, an information letter/leaflet, and the informed consent form and complete the baseline online questionnaire (T0) during a study information meeting with a study assistant.

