### Content of the face-to-face group intervention MoVo-LISA

The psychological group program MoVo-LISA (Motivation-Volition concept to support Lifestyle-Integrated Sports Activity; three to eight patients per group) is based on both motivation theories of health behavior [43–45] and volition theories of action planning and action control [46–48]. The theoretical framework underlying the MoVo-LISA intervention program is the MoVo process model. Its core idea is the differentiation between motivational and volitional strategies [21]. Motivational strategies are used to help form a strong and self-concordant goal intention. Volitional strategies are needed to implement competencies and action control [13]. MoVo-LISA is conceptualized as a short and economical psychological program based on a standardized curriculum. It has been developed specifically for an inpatient rehabilitation setting and has been shown to be effective in orthopedic patients [16, 17, 20]. In this trial, MoVo-LISA is offered to all randomized participants in both the intervention and control groups by the physiotherapists or sport and exercise therapists in each clinic. Before recruitment, all MoVo-LISA instructors were trained in the standardized program by the scientific project team during a 2-day course. In addition, a kickoff meeting was organized for all clinic staff in order to inform them about the study and to familiarize them with the MoVo concept.

The program MoVo-LISA consists of two group sessions and one individual session in which patients learn how to integrate physical activity into their daily lives. It does not consist of actual physical exercise but focuses on teaching the patients how to get and stay physically active after inpatient rehabilitation. The patients prepare specific activity plans for implementation in their everyday lives based on their individual needs and living context. Hence, the activity plans of the participants vary highly from aerobics to stretching and stabilizing exercises and are based on the recommendations that were developed during their orthopedic rehabilitation. In addition, they identify barriers that discourage them from being active and develop individual strategies to cope with those barriers. After discharge from the clinic, participants receive a postal reminder and a telephone interview. A detailed description is given by Fuchs and Göhner [16, 49]. The five main components of MoVo-LISA are listed in Table 1.

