### Control condition

The control group receives MoVo-LISA during the clinic stay and has unrestricted access to TAU.

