### Statistical analyses

The primary outcome of physical activity assessed with the respective subscale of the BSA-F at T4 (post-treatment of MoVo-App) will be analyzed as a dependent variable and its baseline value as a covariate, adjusted for sex and age and potentially other covariates. Continuous secondary outcomes will be analyzed accordingly. The statistical analysis for all research questions will be based on linear mixed-effects models with restricted maximum likelihood estimation to account for missing data [71]. The model is a mixture model, thus assuming two distinct distributions: (1) a binomial model (patients becoming physically active from inactivity and vice versa) and (2) a Gaussian distribution of minutes of physical activity per week for those being physically active. In the linear mixed-effects models, time (T1 to T5) will be the within-subjects factor, and intervention (MoVo-LISA and TAU plus MoVo-App vs. MoVo-LISA and TAU) will be the between-subjects factor. All two-way interactions will be considered. Main effects and interactions will be estimated for time points T3 to T5.

Baseline minutes of sport activity, age, sex, and body mass index will be included as covariates, along with other relevant demographic and clinical characteristics (e.g., disease, pain intensity, pain interference) collected through patient self-report. The model will allow for random intercepts, and all other factors will be treated as fixed effects. All statistical analyses will be performed using R software [72].

We expect to see a skewed distribution in our primary outcome physical activity, and, following guidance [72, 73], we will use transformations or consider using generalized or mixture-distribution mixed models [72]. Effects will be considered significant if *p* < 0.05. Assumptions for general, generalized, or mixture-distribution models will be checked graphically and with tests appropriate to the model [74, 75]. In addition, we will run several model checks by comparing increasingly complex models with different covariance structures, link functions, and estimation procedures with a null model via likelihood ratio tests and comparison of fit via the Akaike information criterion and Schwartz’s Bayesian information criterion [76].

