## Discussion

The present trial focuses on individuals with musculoskeletal conditions. The purpose of the MoVo-App trial is to evaluate a blended intervention of inpatient, face-to-face treatment coupled with a mobile app to help initiate and promote the maintenance of physical activity in this vulnerable patient group. Previous studies have shown that the initial adoption of physical activity is possible and successful in this population. Most studies to date have not succeeded in implementing long-term habit change in participants.

In a rigorous evaluation, this trial addresses some of the gaps of prior studies. First, given that many people have busy lifestyles, they value convenient access to health behavior change programs [79]. In this context, the MoVo-App offers the opportunity to support behavioral interventions in real-life situations. Second, although apps have a high potential to support individuals to become active more sustainably, most of the apps are lacking evidence-based content [80]. In the development of the MoVo-App, we systematically translated the theoretical concepts of the MoVo process model into the app. Third, outcomes in this study not only comprise physical activity behavior but also measure health-related variables (e.g., pain intensity, depression) and underlying psychological mediators of behavior change as postulated within the MoVo concept. This will allow a deeper understanding of the treatment processes within MoVo-LISA and the MoVo-App, which in turn can help to further develop the intervention. Fourth, by implementing the intervention directly into routine healthcare, we will be able to enroll a more naturalistic sample. Most trials of internet- and mobile app–based interventions suffer from a selection bias with mostly highly educated and female participants self-selecting into these interventions [35, 81]. Due to the consecutive routine care sample, self-selection bias can be minimized in this trial. Finally, MoVo-LISA is conceptualized to be used for a wide range of settings and indications. Therefore, the blended intervention of MoVo-LISA and the MoVo-App can easily be transferred to other (healthcare) settings as well as health conditions.

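### Secondary question 3 asks what moderates and mediates the effects of MoVo-LISA, but both arms receive MoVo-LISA, so only moderators and mediators of the added app have a controlled contrast

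*Protocol article*

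**What the plan says.** The third secondary question (protocol article, Background) is: "Which cognitive and sociodemographic factors moderate and mediate the effects of MoVo-LISA and MoVo-App". The Discussion returns to the theme when it explains why psychological mediators are measured: "This will allow a deeper understanding of the treatment processes within MoVo-LISA and the MoVo-App". It adds that this understanding can feed into further development of the intervention.

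The design sections say who receives what:

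- Study design: "All participants receive treatment as usual (TAU) and the face-to-face group-based intervention MoVo-LISA during their clinic stay".
- Content of the face-to-face group intervention MoVo-LISA: "MoVo-LISA is offered to all randomized participants in both the intervention and control groups".
- Control condition: "The control group receives MoVo-LISA during the clinic stay and has unrestricted access to TAU".
- Statistical analyses: "intervention (MoVo-LISA and TAU plus MoVo-App vs. MoVo-LISA and TAU) will be the between-subjects factor".

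For moderation and mediation, the Statistical analyses section extends the mixed model with psychosocial factors. It will estimate three things for each factor: its own contribution as a covariate, its interaction with the intervention group, and its three-way interaction with group and time.

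**The concern.** A moderator or mediator is always a moderator or mediator of some effect, and that effect has to be identifiable first. Question 3 names two components, and only one of them differs between the arms. Read as it stands, half of the objective asks for something that the design cannot deliver.

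What is at stake is the interpretation of secondary results. The planned model produces a main effect for every psychosocial factor. If self-efficacy or action planning predicts activity across both arms, question 3 and the Discussion sentence invite the authors to report it as a moderator or mediator of MoVo-LISA. It would only show that some patients do better than others under a treatment that everyone received. The Discussion envisages using such findings to develop the intervention further.

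**Working it through.** The plan gives no figure to reproduce on this point. The argument is structural, so it takes the design facts, writes out the model and asks which terms can be estimated.

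**Inputs**

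- Planned sample: 224, allocated 1:1 (Proposed sample size/power calculations; Study design).
- Assigned to MoVo-LISA: both arms, so 224 with and 0 without.
- Assigned to the app: intervention arm only, by randomisation.
- Alongside MoVo-LISA in the clinic: a three-week multimodal rehabilitation programme for everyone (Treatment as usual).
- Time factor in the model: T1 to T5, with baseline as a covariate and effects estimated for T3 to T5 (Statistical analyses).

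**Step 1: moderation.** Let A = 1 for the app arm and 0 otherwise, L = 1 for assignment to MoVo-LISA, and M be a candidate moderator. A model able to answer both halves of question 3 would be

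E(Y) = b0 + b1·A + b2·L + b3·M + b4·A·M + b5·L·M.

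Here L = 1 for everyone, so it collapses to

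E(Y) = (b0 + b2) + b1·A + (b3 + b5)·M + b4·A·M.

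The effect of MoVo-LISA (b2) cannot be separated from the intercept. Its moderation (b5) cannot be separated from the prognostic effect of M (b3). The app effect (b1) and its moderation (b4) remain estimable. A numerical check of the six-column design matrix agrees: its rank is 4 of 6. Adding patients does not help, because every new row also has L = 1.

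**Step 2: mediation.** An indirect effect needs the effect of the treatment on the mediator. For the app this is E(M | A = 1) − E(M | A = 0), and both terms are observed under randomisation. For MoVo-LISA it is E(M | L = 1) − E(M | L = 0), and the second term is not observed in this trial. However the mediation model is specified, it has no controlled estimate of the first link for MoVo-LISA.

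**Step 3: the planned terms, one by one.**

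| Planned term | What it estimates | Bears on MoVo-LISA's effect? |
|---|---|---|
| Factor as covariate | Association of the factor with the outcome (b3 + b5 together) | No; prognostic |
| Factor × group | How the app's added effect varies with the factor (b4) | No; app only |
| Factor × group × time | How that variation changes over time | No; app only |

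**Step 4: is there another source?** The documents describe no external control and no separate analysis of MoVo-LISA. An uncontrolled change from admission (T0) to discharge (T1) exists. It coincides with the rehabilitation programme and with elapsed time, and it is not a time contrast in the model, because the time factor starts at T1. The accurate statement is therefore that there is no controlled contrast for MoVo-LISA, not that there are no data at all.

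**The case against.** The strongest reply is that question 3 uses shorthand. Elsewhere the article names the two components together to mean the blended package, and questions 1 and 2 compare that package with MoVo-LISA without the app. This is a fair reading of the intent, but it does not remove the problem. Questions 1 and 2 state the comparator and question 3 does not. Even on the package reading, the comparator contains MoVo-LISA, so only the app's increment is identified. The Discussion sentence also names processes within each component.

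Other parts of the reply do stand, and they rule out stronger readings:

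- A reader might infer that the trial plans to present uncontrolled before-after change as evidence on MoVo-LISA. No section plans this. Time runs from T1, baseline is a covariate, and the planned interactions with group already target the app.
- A reader might add that, because entry requires "being physically inactive (sport activity < 30 min/week) in the last 3 months", floor effects and regression to the mean would produce a rise in both arms. That would threaten a pooled before-after analysis, but none is planned. It does not bias the randomised contrast, and the documents give no figure for its size.
- A reader might extend the point to the aim in Study design of finding out whether the app combined with MoVo-LISA "can effectively support inactive individuals to initiate physical activity". That does not follow. Becoming active can be compared between arms after discharge: active/inactive status is part of the primary outcome in the Abstract, and the planned model has a binomial part for it. This aim needs no change.
- The Discussion sentence is a remark about expected insight, and no analysis or decision rule depends on it. The Background also credits earlier studies with the evidence on MoVo-LISA's effects and mediators.

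**Conclusion.** The point holds for three places: question 3, the Discussion sentence on treatment processes, and the interpretation of the factor main effects in the moderation and mediation model. With 0 of 224 patients assigned to a condition without MoVo-LISA, the effect of MoVo-LISA and its moderators and mediators have no controlled contrast, and sample size has no bearing on this. It rests only on the protocol's own statements of who receives what, with no assumed figure.

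Its reach is limited. It concerns a secondary objective and what may be concluded from it. The primary comparison, the sample size and the planned interactions with group are untouched. It is also separate from how mediation is modelled, since a perfectly specified mediation analysis would still speak only about the app when added to MoVo-LISA. A later analysis plan could narrow the question but could not supply the missing contrast, so this is not a detail that the article has merely left to another document.

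**What to change.** Three changes of wording:

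1. Restate question 3 as: which cognitive and sociodemographic factors moderate and mediate the additional effect of the MoVo-App over MoVo-LISA alone?
2. In the Discussion, limit the sentence on treatment processes to those through which the app adds to MoVo-LISA.
3. In Statistical analyses, add that only the interactions with group, and with group and time, are read as moderation of an intervention effect, namely the app's. Mediation is likewise claimed only for the app. Factor main effects, and any change pooled over arms, are reported as prognostic or descriptive and not as moderation or mediation of MoVo-LISA.

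Recruitment ended in December 2019, so the design cannot be changed, but the claims can. No new data or analyses are needed. The only loss is a secondary claim that the design cannot support.

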## Methods/design

### Study design

This study was registered on the World Health Organization International Clinical Trials Registry Platform via the German Clinical Studies Trial Register on 18 October 2018 (DRKS00014814). For an overview of the study schedule, enrollment, interventions, and assessments, *see* the Standard Protocol Items: Recommendations for Interventional Trials (SPIRIT) [38] schedule in Fig. 1. The SPIRIT checklist [38] can be found in Additional file 1.

**Fig. 1 Fig1:**
[figure not shown]
Schedule of enrollment, interventions, and assessments

This is a multicenter, pragmatic RCT of parallel design with an allocation ratio of 1:1. In this RCT, we aim to evaluate whether the MoVo-App in combination with the group-based face-to-face intervention MoVo-LISA during orthopedic rehabilitation can effectively support inactive individuals to initiate physical activity, to increase their amount of physical activity (minutes per week), and to maintain this level of physical activity (physically active: yes/no and minutes per week) in the long term.

All participants receive treatment as usual (TAU) and the face-to-face group-based intervention MoVo-LISA during their clinic stay (*see* Fig. 1 and the Consolidated Standards of Reporting Trials (CONSORT) flowchart in Fig. 2). After participating in the face-to-face MoVo-LISA program in the clinic, the IG receives the MoVo-App at clinic discharge as a blended intervention. Following eligibility screening by the clinic staff, participants give informed consent and complete baseline outcome assessments prior to randomization and allocation (T0). Assessments are repeated at clinic discharge (T1), at 6 weeks (T2), and at 4 months after discharge (after the end of the MoVo-App and thus post-treatment) (T3), as well as 6 (T4) and 12 months (T5) after discharge (follow-up). All assessments are conducted through online questionnaires. The first two assessments (T0 and T1) take place in the clinic, and the participants are supported by a study assistant. All further online questionnaires are sent to the participants via e-mail. If the participants do not complete the questionnaires, they will be reminded after 2, 4, 6, and about 14 days after receiving the questionnaire. The first and second reminders are sent to the participants by e-mail. The third reminder is carried out via telephone. If the patients cannot be reached by telephone, they are called a second time.

**Fig. 2 Fig2:**
[figure not shown]
Consolidated Standards of Reporting Trials (CONSORT) flowchart

We are conducting and reporting the RCT in accordance with the CONSORT 2010 statement [39], the supplement of the CONSORT statement for pragmatic effectiveness trials [40], and current guidelines for executing and reporting eHealth research [41]. All procedures are approved by the ethics committee of the Albert Ludwig University of Freiburg (no. 270/18).

In a pilot study from October until December 2018, the procedures for recruitment and intervention delivery in the clinics were tested and refined. During this time, 34 participants were recruited. On the basis of experiences and feedback of patients as well as clinic staff regarding conduction and implementation of the study, some adjustments and improvements were made to optimize the recruitment strategies, outcome assessments, and the usability and installation of the MoVo-App.

### Proposed sample size/power calculations

In a previous group-based MoVo-LISA trial with orthopedic patients, exercise duration was 156 min/week immediately after the intervention, which decreased to 92 min/week at 6 months after discharge [16]. If the MoVo-App is able to stabilize the post-treatment effect, a medium effect size of (standardized mean difference) *d* = 0.62 for the main effect and a small to medium effect size for the interaction effect group (MoVo-LISA + MoVo-App) × time of *d* = 0.35 at the 6-month follow-up (T4) can be expected. However, the effect size estimate for the interaction effect could only be extrapolated from interaction effects observed for group trials comparing MoVo-LISA with a wait-list control group [19]. We assume a baseline measure of the outcome to be used as a covariate and a correlation between pre- and postmeasures of 0.33 based on prior data. With a power of 80%, a significance level of 5%, and small to moderate effect sizes, and considering an estimated dropout rate of 15%, a total sample size of 224 is required.

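### The stated 224 participants for 80% power follows from neither planning effect: on a two-sided reading d = 0.35 needs about 270 and d = 0.62 fewer than 90, and the powered contrast is not named

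*Protocol article*

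**What the plan says.** The section on proposed sample size and power starts from an earlier trial of the group programme, in which "exercise duration was 156 min/week immediately after the intervention, which decreased to 92 min/week at 6 months after discharge". On the condition that the app stabilises the post-treatment effect, it expects "a medium effect size of (standardized mean difference) *d* = 0.62 for the main effect" and, for group by time, an effect "of *d* = 0.35 at the 6-month follow-up (T4) can be expected". The two values are joined in one clause, "for the main effect and a small to medium effect size for the interaction effect", under that single condition. The next sentence adds that the interaction estimate "could only be extrapolated from interaction effects observed for group trials comparing MoVo-LISA with a wait-list control group".

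The remaining inputs are a baseline measure used as covariate, a correlation of 0.33 between pre- and postmeasures, and 15% dropout. The requirement is worded "With a power of 80%, a significance level of 5%, and small to moderate effect sizes", and the total is 224. The section gives no SD and no sidedness, and it does not say which of the two effects the 80% refers to.

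Elsewhere in the article, allocation is 1:1 (Study design), and both arms receive the group programme, with the app added at discharge in the intervention arm only (Study design; Control condition). The primary outcome is analysed at T4 with its baseline value as covariate (Statistical analyses).

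**The concern.** A sample size statement should let a reader recover the total from its inputs and tell which contrast carries the stated power. This one prints two effect sizes that differ almost by a factor of two, attaches both to one scenario, and gives a total without saying which effect produced it.

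If 224 was meant for the smaller effect, the power after dropout is below the 80% claimed. If it was meant for the larger, the trial is far larger than that effect requires and the smaller figure plays no part. In either case a reader of the results cannot say what difference the trial was planned to detect, and a non-significant result would be read against a power figure that the design does not deliver for d = 0.35.

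**Working it through.** **Inputs.** From the sample size section: d = 0.62 and d = 0.35, r = 0.33, power 80%, alpha 5%, dropout 15%, total 224. From Study design: 1:1 allocation. Assumption: two-sided test. The section gives no sidedness; a one-sided reading is in step 4.

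**1. Reproducing 224.** For a two-arm comparison of means adjusted for baseline, the total evaluable number is

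N = 4 (z₀.₉₇₅ + z₀.₈₀)² (1 − r²) / d²

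and the number randomised is N / (1 − 0.15). Here (1.960 + 0.842)² = 7.849 and 1 − 0.33² = 0.891.

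- d = 0.62: 4 × 7.849 × 0.891 / 0.3844 = 72.8 evaluable; 72.8 / 0.85 = 85.6, so 86. Rounding up per arm (37 + 37 = 74) gives 74 / 0.85 = 87.1, so 88.
- d = 0.35: 4 × 7.849 × 0.891 / 0.1225 = 228.4 evaluable; 228.4 / 0.85 = 268.7, so 269. Rounding up per arm (115 + 115 = 230) gives 230 / 0.85 = 270.6, so 271.

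Neither gives 224. The nearest figure is the requirement for d = 0.35 before dropout, 228 to 230.

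**2. What 224 delivers.** 224 × 0.85 = 190.4 completers, about 95 per arm. The standard error of the adjusted difference in SD units is √(2 × 0.891 / 95.2) = 0.137.

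- d = 0.35: 0.35 / 0.137 = 2.56; 2.56 − 1.96 = 0.60; power about 72.5% (72.0% with the noncentral t distribution and 95 per arm).
- d = 0.62: 0.62 / 0.137 = 4.53; 4.53 − 1.96 = 2.57; power about 99.5%.
- d = 0.35 with all 224 analysed: about 79%.
- Effect detectable with 80% power: 2.802 × 0.137 = 0.38 (0.386 with the noncentral t).

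**3. The scenario behind the two effects.** Both arms receive the same programme up to discharge and the app starts there, so the expected gap at T1 is zero. If the app arm stays at 156 min/week and controls fall to 92, then:

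- group difference at T4: 156 − 92 = 64 min/week;
- group by time from T1 to T4: (156 − 156) − (92 − 156) = 64 min/week.

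On any single SD these give the same standardised value, so 0.62 and 0.35 cannot both describe full stabilisation at T4. The size of that SD does not matter for this step. If 0.62 is 64 / SD, the SD would be about 103 min/week, but the article does not give it. Dividing by the SD of change instead, with r = 0.33, gives 0.62 / √(2 × 0.67) = 0.54, still not 0.35.

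**4. Other readings.** All include 15% dropout.

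| Reading | d = 0.35 | d = 0.62 |
|---|---|---|
| Two-sided, no covariate | 304 | 97 |
| One-sided, with covariate | 212 | 69 |
| One-sided, no covariate | 238 | 78 |
| Two-sided, change score | 405 | not needed |

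Averaged or repeated-measures tests give at most 205 for d = 0.35. No variant tried that includes dropout falls within 3% of 224 (217 to 231).

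**The case against.** The strongest defence is that the section discloses where the 0.35 comes from. It was carried over from wait-list trials and not computed from 156 versus 92, so it can be read as a deliberately cautious second value. The larger value, read as the group difference at T4, fits the stabilisation scenario. This stands, and it reduces the conflict between the two effects to loose wording: both are placed under the same condition when only one belongs there. It does not explain 224.

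A reader might go further and infer that the two labels are swapped, because a main effect averaged over visits would come out near 0.35. The article does not support that. With an assumed SD of 103, linear divergence to T4 and a plateau at T5, averaging over T1 to T5 gives (0 + 16 + 32 + 64 + 64) / 5 = 35.2 min, or 0.34; with T3 at 4 months it gives 0.36. The Statistical analyses section, however, says "Main effects and interactions will be estimated for time points T3 to T5". Over that window the same path gives 0.52 (T3 at 3 months) to 0.55 (T3 at 4 months). Other time courses run from 0.27 upwards. The trajectory and the SD are both assumptions, and the section does not define the main effect as an average over visits. It follows neither that the powered effect was mislabelled nor that 0.62 must be removed.

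Sidedness is the second defence. A one-sided 5% test would give about 82% power for d = 0.35 with 95 per arm. Nothing in the article announces a one-sided test, the planned intervals are 95%, and that reading gives 212, not 224. It is a reason to state the sidedness.

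A mixed model also uses earlier visits of people who drop out, which may recover some power. The correlations needed to quantify this are not given. Finally, the planned standardised differences with 95% confidence intervals keep a null result interpretable in part, which tempers the consequence without repairing the power statement.

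**Conclusion.** The point holds for the total and for the unnamed contrast. Assuming a two-sided 5% test, baseline adjustment with r = 0.33 and 15% loss, 224 falls 45 to 47 short of what d = 0.35 requires (269 − 224; 271 − 224) and is more than two and a half times what d = 0.62 requires (224 / 86 = 2.6; 224 / 88 = 2.5). The stated 80% is about 72% for the smaller effect and over 99% for the larger.

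That 224 lies close to the uninflated requirement for d = 0.35 may suggest that dropout was left out. This is only an inference, since the section says dropout was considered. The two effects do not both follow from full stabilisation, but the text itself attributes the smaller one to another source, so this part is a matter of wording. It should be corrected; it does not invalidate the design.

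**What to change.** Rewrite the paragraph around one powered contrast: the group difference in sport activity at T4, adjusted for baseline. Give its d, the sidedness of the test, r = 0.33 and the 15% dropout. Keep 0.62 as the value attached to full stabilisation if its SD can be stated. Present 0.35 separately, as a cautious assumption taken from the wait-list trials and not as a consequence of stabilisation. Then restate what 224 provides: about 72% power for d = 0.35 after 15% dropout, or 80% power for d of about 0.38 to 0.39, both two-sided. If another method produced 224, name it and its inputs so that the figure can be recovered.

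Recruitment closed in December 2019 and no further enrolment is needed. The cost is one paragraph and a less favourable stated power.
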